## Abstract

**Background:**

Recently, clinical observations reported the potential benefit of vagus nerve stimulation (VNS) for pediatric epilepsy. Transcutaneous auricular vagus nerve stimulation (ta-VNS) is a newer non-invasive VNS, making it more accessible for treating pediatric epilepsy, yet there is limited clinical evidence for its effectiveness.

**Methods/Design:**

A three-center, randomized, parallel, controlled trial will be carried out to evaluate whether ta-VNS improves pediatric epilepsy. Pediatric patients aged 2 to 14 years with epilepsy will be recruited and randomly assigned to transcutaneous auricular vagus nerve stimulation (ta-VNS) group, transcutaneous auricular non-vagus nerve stimulation (tan-VNS) group, and control group with a 1:1: sqrt(2) allocation, as per a computer generated randomization schedule stratified by study center using permuted blocks of random sizes. We will use Zelen’s design, in which randomization occurs before informed consent. Patients in the stimulation groups will receive tan-VNS or ta-VNS three times a day for 6 months. Patients in the control group will not be provided with any stimulation during the 6 months. The guardians of the patients are required to keep a detailed diary to record the data. Outcome assessment including seizure frequency, electroencephalogram (EEG), heart rate variability (HRV) analysis, quality of life (QOL) and adverse events will be made at baseline and 2, 4 and 6 months after ta-VNS initiation. The seizure frequency and adverse events will be followed up at 1 year and 1.5 years after ta-VNS initiation.

**Discussion:**

Results of this trial will help clarify whether ta-VNS treatment is beneficial for pediatric patients, and will make clear whether the anticonvulsive effect of ta-VNS is correlated with the improvement of sympathovagal imbalance.

**Trial registration:**

Clinical Trials Identifier: NCT02004340. Registration date: 13 November 2013.

**Electronic supplementary material:**

The online version of this article (doi:10.1186/s13063-015-0906-8) contains supplementary material, which is available to authorized users.

## Background

Vagus nerve stimulation (VNS) has been approved by US Food and Drug Administration (FDA) as a complementary treatment for partial refractory epilepsy in patients aged no less than 12 years, since 1997 [1]. Recently, clinical observations indicated the potential benefit of VNS for pediatric epilepsy. In a retrospective review of patients undergoing VNS insertion, it was suggested that VNS is a safe and effective adjuvant therapy for children under 12 years old, with over half reporting significant benefit [2]. Clinical results reported by the Pediatric VNS Study Group showed a median reduction in seizure frequency of 42 % after 18 months of intermittent stimulation of the left vagal nerve [3].

Recently, newer non-invasive VNS has improved the safety and tolerability of VNS, making it more accessible and facilitating further investigations across a wider range of uses [4]. Transcutaneous auricular vagus nerve stimulation (ta-VNS) at the innervation area of the auricular branch of the vagus nerve (ABVN) has been utilized in the treatment of epilepsy. In a pilot study of adult patients, after 24 weeks’ treatment of ta-VNS, 8/47 patients were seizure-free; 19/47 patients had reduced seizure frequency [5]. It has also been reported that ta-VNS can effectively reduce the frequency of seizures and improve the patient’s quality of life in adult epilepsy patients [6]. In our pilot trial of ta-VNS for pediatric epilepsy, mean reduction in seizure frequency relative to baseline was 54.13 % at the end of 24 weeks’ treatment [7]. Yet no randomized controlled trial (RCT) has been performed on the safety and efficacy of ta-VNS for patients with pediatric epilepsy.

Autonomic imbalance has been found to be accompanied with epilepsy. An increased sympathetic activity and reduced parasympathetic activity were observed in patients with epilepsy [8, 9]. In children with refractory epilepsy, parasympathetic activity is lower in comparison with healthy controls [10]. A systematic review confirmed a sympathovagal imbalance in epilepsy, as shown by lower high-frequency (HF) power spectrum, standard deviation of normal-to-normal interval (SDNN) and root mean square of successive differences (RMSSD) values when compared to controls [11].

In the present study, we use transcutaneous auricular non-vagus nerve stimulation (tan-VNS) as a sham comparator, waiting list group as a control. We aim to investigate the safety and efficacy of ta-VNS in treating pediatric patients with epilepsy in a multicenter RCT, and determine whether the anticonvulsive effect of ta-VNS is correlated with the improvement of sympathovagal imbalance.

## Methods

### Study design

A multicenter randomized, parallel, controlled trial is currently being performed. Pediatric patients will be included from three centers, including Beijing Tiantan Hospital and Beijing Children Hospital affiliated to Capital Medical University, and Acupuncture Hospital affiliated to the Institute of Acupuncture and Moxibustion, China Academy of Chinese Medical Sciences. The protocol has been approved by the Clinical Trial Ethics Committee of the Institute of Acupuncture and Moxibustion, China Academy of Chinese Medical Sciences (number: 2012030101) and registered on ClinicalTrials.gov protocol registration system (Clinical Trials Identifier: NCT02004340). Informed consent will be sought from all the guardians of the participants.

At the beginning of the enrollment, participants in the control group will be given a diary book to record the data, including the frequency of seizures and adverse events. Participants in the stimulation groups will be given a ta-VNS instrument and a diary book to record the frequency of seizures, usage of instruments and side-effects or adverse events. Patients or their guardians will be required to keep a detailed diary. This trial will include a 6-month treatment period and a 1.5-year follow-up period. Outcome assessment of ta-VNS will be made at baseline and 2, 4 and 6 months, 1 year and 1.5 years after ta-VNS initiation (Fig. 1).

**Fig. 1 Fig1:**
[figure not shown]
Trial flow chart

### Inclusion criteria

Participants will be included if they meet all of the following conditions: 1) diagnosis of epilepsy, and aged between 2 and 14 years old; 2) the number and dose of the medication has been kept constant no less than 2 months before intervention; 3) the number of epileptic seizures is no less than eight in 2 months; 4) the patients or their guardians can count the frequency of the seizures and finish the study; and 5) the guardians can understand the mechanism of the ta-VNS treatment, voluntarily agree with the study protocol and sign written informed consents.

### Exclusion criteria

Participants will be excluded if they meet any of the following conditions: 1) the patient is receiving VNS therapy; 2) the patient is accompanied with progressive central nervous disease; 3) the patient has severe heart, liver or blood disease; or 4) previous participation in this study.

### Randomization and blinding

Participants will be randomly assigned to either one of the two stimulations or the control group with a 1:1: sqrt(2) allocation, as per a computer generated randomization schedule stratified by the study center using permuted blocks of random sizes. The block sizes will not be disclosed, to ensure concealment. We will use Zelen’s design, in which randomization occurs before informed consent. Those patients in the control group (n = 42) receiving standard care will not be consented for participation in this study. They will be informed in an observational study with questionnaires to provide the same measurements, except for treatment, as that in the treatment groups for free, and thus blinded. Other participants who accept the intervention will provide further informed consents, in which they will be informed to have the possibility of receiving either one of the two stimulations according to computerized randomization schedule. The two stimulation groups will include the tan-VNS group (n = 30) and the ta-VNS group (n = 30). Participants in the control group and stimulation groups are thus blinded.

The randomization sequence will be generated using SPSS v.17.0 software (IBM, Armonk, NY, USA) and distributed in a sealed envelope to the doctor. The researchers will not be permitted to change it after the patients are randomized. Employees outside the research team will feed original data into the computer in separate datasheets so that the researchers can analyze data without having access to information about the allocation. The evaluation of the curative effect and the statistical analysis will be evaluated by a third party in the clinical evaluation center of the China Academy of Chinese Medical Sciences who will not know the grouping and patients. In this clinical trial process, the patients, statisticians and the assessor for statistical data and outcomes will be blind to treatment allocation. Allocation concealment will not be exposed until the final data analysis report is completed.

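### All three arms are randomized before consent although ta-VNS and sham families sign the same consent, and the consent rules make eligibility depend on the arm

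*Protocol article*

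**What the plan says.** Randomization and blinding describes a single allocation: "Participants will be randomly assigned to either one of the two stimulations or the control group with a 1:1: sqrt(2) allocation". It adopts Zelen's design, "in which randomization occurs before informed consent", and makes no exception for the split between the two stimulation arms. Sequences are "distributed in a sealed envelope to the doctor". The same section lists patients, statisticians and the outcome assessor as blind; the doctor is not on that list.

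Consent then differs by allocation. Control patients "receiving standard care will not be consented for participation in this study" and are told only of an observational study. For the stimulation arms, "Other participants who accept the intervention will provide further informed consents", and in that consent "they will be informed to have the possibility of receiving either one of the two stimulations according to computerized randomization schedule". The content is thus the same for ta-VNS and tan-VNS.

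Other sections state a different rule. Study design says: "Informed consent will be sought from all the guardians of the participants". Inclusion criterion 5 requires guardians to understand how ta-VNS works and to "voluntarily agree with the study protocol and sign written informed consents". Table 1 marks informed consent at baseline without distinguishing arms. Quality control and trial monitoring adds that enrolled families should understand the ta-VNS mechanism and the team's earlier results.

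Statistical analysis defines the intention-to-treat population as randomized participants with at least one treatment session.

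**The concern.** There are two separate problems, and they affect different contrasts.

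The first concerns ta-VNS versus tan-VNS, the comparison that isolates the vagal effect. Zelen's design has a purpose here: it keeps controls unaware of a treatment they will not receive. That purpose is met once stimulation is separated from control. Allocating between two stimulations before a consent that is identical for both gains nothing. It places refusals after the randomization that should protect this comparison, and the analysis population then removes them.

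The second concerns stimulation versus control. If signed consent and understanding of ta-VNS are entry criteria, controls who are never told of the trial cannot meet them. In practice the criterion would operate only in the stimulation arms, after allocation. Those arms would then hold families willing and able to accept home stimulation, while the control arm would hold everyone allocated to it.

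**Working it through.** **Allocation figures.** The arm sizes are 30, 30 and 42 (total 102). 30 × √2 = 42.4, and 102/(2 + √2) = 29.9 with 29.9 × √2 = 42.2. The stated sizes agree with 1:1:√2. The article gives no power, effect size, SD or refusal rate, so there is no planned power to reproduce.

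**Consent rules side by side.**

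| Place | Who consents |
|---|---|
| Study design | all guardians |
| Inclusion criterion 5 | every participant's guardian, with understanding of ta-VNS |
| Table 1 | all patients, no arm distinction |
| Randomization and blinding | stimulation arms after allocation; controls not consented to this study |

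The first three rows cannot hold together with the fourth. If the fourth governs, criterion 5 fails for all 42 controls and filters only the 60 stimulation patients.

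**Where refusals fall.** The order for stimulation patients is: allocation to a specific arm, consent offered, acceptance or refusal, first session, entry to the analysis population. Refusers drop out between allocation and analysis.

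**Power, if 30 per arm means randomized.** Assume a standardized effect d that gives 80% power with 30 per arm at two-sided 5%: d = √(2/30) × (1.960 + 0.842) = 0.723. With a proportion r refusing in each arm and excluded, n = 30(1 − r) and power = Φ(d/√(2/n) − 1.960):

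| r (assumed) | n per arm | power |
|---|---|---|
| 0% | 30 | 80.0% |
| 10% | 27 | 75.7% |
| 20% | 24 | 70.7% |
| 30% | 21 | 65.0% |
| 40% | 18 | 58.3% |

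If 30 means accepted, this loss is nil.

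**Bias, if the arm is known when consent is sought.** Let refusers differ from acceptors by D SD in outcome, with refusal proportions r₁ and r₂. With no treatment effect, the difference between acceptors is (r₂ − r₁) × D.

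- Equal refusal (20% v 20%) for the same reasons: bias 0, type I error 5.0%.
- 10% v 25%, D = 0.5: 0.15 × 0.5 = 0.075 SD. With 27 and 22.5 analysed, SE = √(1/27 + 1/22.5) = 0.285, shift 0.075/0.285 = 0.26, type I error about 5.8%.
- 10% v 30%, D = 0.5 to 1.0: bias 0.10 to 0.20 SD, type I error 6.4% to 10.6%.

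Every refusal proportion and every D here is an assumption. Type I errors use the normal approximation.

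**The case against.** A reader might infer that the contradictory consent rules themselves damage ta-VNS versus sham. The text does not support that: both stimulation arms face the same criterion 5 and the same consent, so the contradiction bears on stimulation versus control only.

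A reader might also infer that the sham contrast is biased as it stands. That needs the person seeking consent to know the arm. The envelope is sealed, the article does not say when it is opened, and the mention of a computerized schedule in the stimulation consent could be read as an assignment made or disclosed after signing. The article also refers to an additional file for more detail. This objection stands as far as bias is concerned. It does not remove the point: only one three-arm schedule is described, randomization is said to precede consent, and someone must learn that a patient is not a control before offering stimulation consent. With a single three-arm envelope, the same act can reveal which stimulation it is.

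A third tempting step is to compute dilution with refusers kept as untreated patients. The planned population excludes them, so such figures describe an analysis this trial does not plan. Nor is a power loss certain under exclusion, because the 30 and 30 appear directly after the sentence on those who accept.

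Finally, the consent rules can be partly reconciled. The word *further* suggests an earlier agreement, so Study design could mean observational consent from all and stimulation consent from some. That reading does not rescue criterion 5, which asks every guardian to understand ta-VNS and agree with the protocol.

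**Conclusion.** The point holds in two parts.

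For ta-VNS versus tan-VNS, allocating before a common consent is unnecessary and lets refusals remove patients after randomization. If the arm is concealed at consent, the result is restriction to acceptors, with a power loss only if 30 per arm means randomized. If it is not concealed, bias is possible; 0.075 SD illustrates its size under 10% versus 25% refusal and a 0.5 SD difference. The article supports neither a claim that bias is present nor any specific loss.

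For stimulation versus control, the contradiction is in the current text and needs no assumption. Taken literally, controls are ineligible and criterion 5 selects patients in the stimulation arms only, after allocation. The resulting bias cannot be sized from the article.

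**What to change.** 1. Randomize in two steps. First allocate to stimulation pool or control, at 2:√2 to preserve the present ratio. After the guardian has signed the common stimulation consent, randomize 1:1 to ta-VNS or tan-VNS from a second concealed sequence blocked within center. Consent refusals then fall before the sham split. State whether 30 per arm means randomized or accepted; if 60 consenters are wanted, the pool needs 60/(1 − r) patients, for example 75 at an assumed 20% refusal.

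2. Reconcile Study design, inclusion criterion 5, Randomization and blinding, and Table 1. The criteria applied before randomization should be the same for all arms, with observational-data consent for every family and stimulation consent for the pool only.

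3. Report refusals at each step. Flag patients enrolled under the single-step scheme (35 of a planned 102 had been recruited by 15 February 2015) and examine them in a sensitivity analysis.

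The cost is a second envelope series and an ethics amendment. The change does not remove refusals from stimulation versus control, where they are inherent in Zelen's design; there, common eligibility criteria and reporting by step make them visible.

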### Quality control and trial monitoring

Before the initiation of the trial, the researcher will formulate an investigator’s brochure, standard operating procedures and detailed research plan. All the staff should participate in special training, including enrolling patients, completing the case report form and usage of the stimulator. The data monitoring committee has been established, which is independent from the sponsor and competing interests. Monitors will check case report forms at the participating hospitals once a month. Drop-outs and withdrawals (and the reasons) from the study will be fully documented throughout. All the data, including the case report forms and electronic documents, will be kept by special staff. The trial sponsor (BZ) has access to the final trial dataset.

The final report will follow the Consolidated Standards of Reporting Trials (CONSORT) extension guideline for non-pharmaceutical interventions. In order to minimize 6 months’ attrition, first we will enrol patients whose guardians can understand the mechanism of the ta-VNS treatment and our previous results. Second, in the consent inform, the participant and their guardian will be informed that the patient can get doctor consultation during the whole study period. They can also get a physical examination (EEG and HRV) and an auricular vagus nerve stimulator for free when they complete the study. The doctor will keep in touch with the patients once a month by phone or email. Additional file 1 describes the protocol in more detail.

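### All participants are called blinded, but stimulated families know they are treated and may keep the primary-outcome diary; the entry wording also puts masking of the sham at risk

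*Protocol article*

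**What the plan says.** The section Randomization and blinding concludes "Participants in the control group and stimulation groups are thus blinded" and adds that "the patients, statisticians and the assessor for statistical data and outcomes will be blind to treatment allocation".

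The same section sets out what families are told. For those in the stimulation arms, "they will be informed to have the possibility of receiving either one of the two stimulations according to computerized randomization schedule". Controls are not consented for the trial; of them it says "They will be informed in an observational study with questionnaires to provide the same measurements, except for treatment".

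Under Interventions, the active arm is stimulated at the concha and the sham arm at the margin of the auricle, which the article describes as outside the territory of the auricular vagal branch. Technicians train patients or guardians, who then use the device at home three times a day for 6 months. Controls get no device.

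The primary outcome is seizure frequency counted from the diary (Primary outcomes). Patients or guardians keep that diary (Study design) and must be able to count the seizures (Inclusion criteria, criterion 4).

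Criterion 5 requires that "the guardians can understand the mechanism of the ta-VNS treatment, voluntarily agree with the study protocol and sign written informed consents". Under Quality control and trial monitoring, the first measure against attrition is "first we will enrol patients whose guardians can understand the mechanism of the ta-VNS treatment and our previous results".

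**The concern.** Withholding the existence of a treatment from controls does not hide treatment from those who receive it. A family that applies a stimulator three times a day knows its child is treated, may expect benefit, and may also count the seizures. The masked third-party evaluator and the separate data entry act only after the diary has been written. They cannot remove bias already in it.

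The sham comparison is the one that could control expectation, and it has a weak point of its own. The two sites look different and the family places the electrodes. Masking therefore rests on guardians not knowing which site is expected to work. The entry and retention wording favours guardians able to grasp how ta-VNS works and what the earlier results were; the Background gives the pilot result as a 54.13% mean reduction in seizure frequency. A guardian who links the mechanism to the concha could recognise an electrode on the margin as the sham.

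At stake is what a positive result would mean. A difference from control would include placebo response and reporting. A difference from sham would be convincing only as far as masking held.

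**Working it through.** **Allocation figure.** The only figure in the blinding section that can be reproduced is the control arm size: 30 × √2 = 42.43, stated as 42, total 30 + 30 + 42 = 102. It agrees. The point does not depend on it.

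**Who knows what, from the text.**

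| Family | Told | Knows whether the child is stimulated? | Knows active from sham? |
|---|---|---|---|
| ta-VNS | one of two stimulations | yes | not stated; site visible |
| tan-VNS | one of two stimulations | yes | not stated; site visible |
| Control | observational study | unaware of a trial, if this is all they are told | not applicable |

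The claim that every group is blinded fails in the first two rows for stimulation versus control. For ta-VNS versus tan-VNS it is possible but not secured.

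**Control-arm statements side by side.** Randomization and blinding says controls are not consented and hear only of an observational study. Study design seeks informed consent from all guardians of participants. Criterion 5 requires every participant's guardian to understand ta-VNS and sign. The Background describes the "waiting list group as a control". Quality control and trial monitoring says the consent information offers "an auricular vagus nerve stimulator for free when they complete the study", with no arm excepted. If criterion 5 covers controls, they are not naive. If it does not, it is wrong as written.

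**Illustrative size, sham contrast.** The documents give no SD, correlation or bias. Assumed: log-scale SD 1, baseline correlation 0.7, no true effect, sham recognised, reported counts 10% to 20% lower under ta-VNS, two-sided 5% test (the plan gives P < 0.05 without sidedness). From the plan: 30 per arm. The shifts are ln 0.9 = −0.105 and ln 0.8 = −0.223. With d = |shift|/SE, the rejection probability is Φ(d − 1.96) + Φ(−d − 1.96).

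| Analysis | SE | d at 10%, 20% | Rejection at 10%, 20% |
|---|---|---|---|
| Post-treatment values, unadjusted | √(2/30) = 0.258 | 0.41, 0.86 | 6.9%, 13.9% |
| Change scores | √(2/30) × √(2 × (1 − 0.7)) = 0.200 | 0.53, 1.12 | 8.2%, 20.0% |
| Baseline-adjusted | √(2/30) × √(1 − 0.49) = 0.184 | 0.57, 1.21 | 8.8%, 22.7% |

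The Statistical analysis section plans one-way ANOVA with post-hoc tests, or Mann–Whitney, and no baseline adjustment. The last row is therefore not the planned analysis.

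**Illustrative size, control contrast.** With 30 versus 42, SE = √(1/30 + 1/42) = 0.239 SD. Assumed reporting shifts of 0.2, 0.3 and 0.5 SD give rejection rates of 13.3%, 24.1% and 55.2%.

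**The case against.** Several parts of the case on the other side stand.

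- A reader might infer that guardians are taught which site works and that the sham is thereby exposed. The documents do not say so. They require guardians who can understand the mechanism and results. A mechanism can be explained as stimulating a nerve through the ear without naming a site, and the consent wording described for the stimulation arms is neutral. The information sheet and training script are not shown. Sham exposure is a risk, not a demonstrated failure.
- A reader might call the control comparison open-label. That goes too far: controls are described as told only of an observational study, and outcome evaluators and statisticians are masked. The unmasking is of stimulated families.
- The free-stimulator offer may belong only to the stimulation-arm consent, and the waiting-list label is a design description that does not show what controls hear. Neither proves a contradiction. The firmer conflict is signed consent from all guardians against controls who are not consented.
- The false-positive figures rest on assumed inputs and on a fully recognised sham, which is the very point in doubt.

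None of this rescues the blinding statement for stimulation versus control, which fails on the section's own account of what families are told.

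**Conclusion.** The point holds in two parts of different strength. It is certain from the text that the statement that all groups are blinded is wrong for stimulation versus control: treated families know they are treated, and the primary outcome is a diary kept by patients or guardians. That contrast measures effect together with expectation and cannot separate them. It is a document-based risk that masking between ta-VNS and tan-VNS is weakened by the entry and retention wording, given visibly different sites and self-application.

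The size is unknown. On the stated assumptions the sham contrast's false-positive rate would be about 7% to 14% for unadjusted post-treatment values, 8% to 20% for change scores and 9% to 23% with baseline adjustment, against a nominal 5%. These are illustrations, not estimates of this trial's error rate, and the conclusion stands without them.

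**What to change.** 1. In Randomization and blinding, say who is masked to what: stimulation-arm families are not masked to stimulation versus control, controls are told only of an observational study, and evaluators and statisticians are masked.
2. Rest the efficacy claim on ta-VNS versus tan-VNS. Report comparisons with control as including placebo response.
3. In criterion 5 and in Quality control and trial monitoring, replace the mechanism and previous-results wording with the ability to operate the stimulator and keep the diary.
4. Describe the two ear sites neutrally in the information sheet and training script, without naming the site expected to be active.
5. Reconcile the consent required of all guardians (Study design, criterion 5), the waiting-list label and the free-stimulator offer with the statement that controls are not consented and hear only of an observational study.

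The cost is an amendment to the protocol, consent text and training script, and the loss of a blinding claim for the control contrast. Trial status reports 35 participants recruited by 15 February 2015. Against the planned 102 that left 102 − 35 = 67 at that date who could receive the new wording. What the first 35 were told cannot be undone, so the cohorts will be informed differently and a sensitivity analysis by consent version is sensible.

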### Outcome measures

#### Primary outcomes

Seizure frequency: the baseline seizure frequency and the seizure frequency after 2 months, 4 months and 6 months of enrollment will be counted according to the patient’s seizure diary. Seizure outcomes will be expressed with a modified Engel scale [12].

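### Arm sizes of 30, 30 and 42 reveal the control arm to the statistician, and usage entries in the seizure diary could reveal device users to the assessor

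*Protocol article*

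**What the plan says.** Under Randomization and blinding, the protocol article says that "the patients, statisticians and the assessor for statistical data and outcomes will be blind to treatment allocation", with no exception for any contrast. The Statistical analysis section also describes the independent interim statistician as blinded to allocation.

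The same blinding section fixes unequal arms: "Participants will be randomly assigned to either one of the two stimulations or the control group with a 1:1: sqrt(2) allocation". The sizes follow: "Those patients in the control group (n = 42) receiving standard care will not be consented for participation in this study", and "The two stimulation groups will include the tan-VNS group (n = 30) and the ta-VNS group (n = 30").

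The Study design section gives the arms different diaries. In the control arm, "participants in the control group will be given a diary book to record the data, including the frequency of seizures and adverse events". Families in the stimulation arms receive the instrument and "a diary book to record the frequency of seizures, usage of instruments and side-effects or adverse events".

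Under Primary outcomes, seizure frequency at baseline and at 2, 4 and 6 months "will be counted according to the patient’s seizure diary", and "Seizure outcomes will be expressed with a modified Engel scale".

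Two safeguards are named. Staff outside the research team key the original data into separate datasheets. A third party that is said not to know the groups or the patients then evaluates the effect and runs the statistics.

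**The concern.** Masking of assessor and analyst is claimed for all three arms, but two design features bear on whether it can hold against the control arm. The first is the arm sizes, which an analyst sees as soon as coded groups are tabulated. The second is the diary: only the stimulation arms have usage entries, and these sit in the same book as the seizure counts.

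At stake are the two stimulation-versus-control contrasts. A reader of the eventual report would credit them with masked outcome classification and masked analysis. If the analyst can tell which code is the control, masking no longer guards against analysis choices made in the light of the results for those contrasts. If the assessor can see who has a device, assignment to an outcome class could be influenced by that knowledge.

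This point concerns the third-party assessor and the statisticians. It does not concern families or the treating doctor.

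**Working it through.** **1. The plan's own sizes.** Inputs are the 1:1:sqrt(2) ratio and 30 children per stimulation arm (Randomization and blinding).

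- Control size: 30 × sqrt(2) = 42.43, which agrees with the stated 42.
- Total: 30 + 30 + 42 = 102.
- Shares: 42/102 = 41.2% for control and 30/102 = 29.4% for each stimulation arm. Control is 42/30 = 1.4 times as large as either.

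Under labels A, B and C, the group of 42 is the control by design. The two groups of 30 cannot be told apart by size.

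**2. Does loss of patients hide the control arm?** Dropout matters only if lost children disappear from the analyst's file. The article gives no dropout figure, so 0 to 30% is assumed. Let each child be retained independently with probability 1 − d, giving retained numbers C for control and A and B for the stimulation arms.

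- C ~ Binomial(42, 1 − d); A and B ~ Binomial(30, 1 − d).
- P(control strictly largest) = Σ over c of P(C = c) × [P(A ≤ c − 1)]².

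For the interim, half of 102 is 51, taken as 21, 15 and 15. If only control loses children, the probability is P(C > 30) at the end and P(C > 15) at the interim.

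| Assumed dropout d | Equal loss, end | Equal loss, interim | Control-only loss, end | Control-only loss, interim |
|---|---|---|---|---|
| 0% | 100% | 100% | 100% | 100% |
| 10% | 99.99% | 99.3% | 99.9% | 98.6% |
| 20% | 99.3% | 94.0% | 88.2% | 76.9% |
| 30% | 96.3% | 85.9% | 36.3% | 36.3% |

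The interim columns take the split as exactly 21/15/15. Block sizes are undisclosed and centers may recruit unequally, so the real split could differ. With full retention, three equal centers and several assumed block sizes, simulated permuted-block lists made control strictly the largest in 94.0 to 99.9% of cases at 51 children. Chance imbalance and dropout together would lower the interim figures somewhat.

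**3. Does arm size reach the assessor?** No. Someone classifying one child's record sees no group totals. The calculation in step 2 applies only to a person who holds arm-coded data.

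**4. Does the diary reach the assessor?** Set side by side, the sections show:

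- The stimulation diary holds seizures, usage and side-effects; the control diary holds seizures and adverse events (Study design).
- The primary outcome is counted from the diary (Primary outcomes).
- Outside staff key the data into separate datasheets before the third party works on them (Randomization and blinding).

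The first two make the original diary, or any extract that keeps the usage field, revealing. The third could prevent this, but only if usage is left out of what the third party receives. The article does not say whether it is. This route is therefore conditional.

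**5. ta-VNS versus tan-VNS.** Both arms have 30 children, a device and the same diary. Neither route separates them.

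**The case against.** A reader might infer that assessor and statistician are both unmasked, so that no protection exists for the control contrasts. The article does not support that. It nowhere says that the third party reads the original diaries or receives usage data, and its separate datasheets and third-party evaluation point the other way. Which fields are released is a detail that an article may leave to the fuller protocol. This part of the objection stands: for the assessor, the document shows a risk and not a breach.

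It is also fair that the size of any resulting bias cannot be estimated. Families make the seizure entries, the article defines no responder threshold, and it gives no sign of how much judgment the third party exercises in assigning an outcome class. Any figure for children moved across a class boundary would be invented, and none is offered here.

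The dropout objection stands in part. Heavy loss confined to control could hide that arm, as the last two columns of the table show. Such loss is not something the plan can rely on for masking.

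The objection does not rescue the statistician's claim. The article itself states the arm sizes, and no separate analysis plan can make an arm of 42 look like one of 30.

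**Conclusion.** The blinding statement claims more than the design delivers.

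- **Statistician, stimulation versus control:** the claim does not hold. With equal dropout of 0 to 30%, coded groups reveal control by size in about 96 to 100% of cases at the end and 86 to 100% at the interim. With loss in control alone, this falls to 88.2% (end) and 76.9% (interim) at 20% loss, and to 36.3% at both at 30% loss.
- **Assessor, stimulation versus control:** the claim holds only if the diary's usage entries are kept from the assessor, which the article leaves open.
- **ta-VNS versus tan-VNS:** masking is not affected by either route.

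The percentages rest on assumed dropout, independent losses and, at the interim, an exact 21/15/15 split. The qualitative conclusion for the statistician rests only on the stated sizes. The point merits a change because the two control contrasts would otherwise be reported with a protection that one party lacks and the other may lack.

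**What to change.** 1. Have the outside data-entry staff extract the seizure entries in one identical format for all three arms, and give the third party only those coded data.
2. Release usage and device side-effect fields to the third party only after the seizure classification and the between-arm analysis are locked. This rule concerns the third party's efficacy file; side-effects are still reported to the doctor as now.
3. Restate the sentences in Randomization and blinding and in Statistical analysis so that the statistician, including at the interim, is said to be blind to ta-VNS versus tan-VNS only. Say that protection for the control contrasts rests on an analysis fixed in advance and on masked seizure classification.

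The cost is a data-release rule and a slightly less favorable blinding statement. The diary need not be redesigned. With 35 participants already recruited (Trial status), changing the primary-outcome instrument mid-trial would be a larger step than the problem calls for, and the extraction can be applied to their diaries too.
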